#### Integration of clinical and − omics data

2.2.8

With the purpose of understanding the molecular mechanisms of TR and identifying potential biomarkers to be used as features in a predictive model of treatment response (TR), we use multi-staged strategies such as differential gene/miRNA expression (limma), knowledge-driven miRNA-target analysis and Weighted Gene Co-expression Network Analysis (WGCNA), as explained previously. Nonetheless, given that we have three different omics layers (DNA, RNA miRNA), we also take advantage of meta-dimensional methodologies, which involve analyzing all omics layers simultaneously. These methodologies are especially powerful to capture complex interactions between the individual molecular layers and possibly identify new integrated molecular features (reduced dimensionality) that explain the phenotype. These new features are then being assessed, as features for a predictive model. We will employ different methods including iClusterPlus, which uses penalized likelihood approach with lasso penalty to associate a genomic feature with a phenotype, multi-omics factor analysis (MOFA), which infers an interpretable low-dimensional data representation as hidden factors or the partial least squares discriminant analysis (PLS-DA), implemented in mixOmics, which has increasingly been used in omics research as a supervised version of PCA that preserves in its first PC as much covariance as possible between the original data and its labeling (30). To avoid overfitting of the algorithm, this discovery analysis is done on two thirds of the Phase 1 data, keeping one third unseen from any training process.

Importantly, given the high relevance of the sex dimension in TR, we will stratify all analyses according to sex. This might as well help to further decipher the influence of sex on TRD. We also clinically assessed anxiety disorders in comorbidity, more frequently present in women, and will be analyzed with respect to omics data and putative sex effect.

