## Introduction

1

The World Health Organization (WHO) declared that “there is no health without mental health.” Mental health is a state of well-being in which an individual is aware of his or her own abilities, can cope with the normal stress of life, can work productively and is able to contribute to his or her community. Major depressive disorder (MDD) is the most common psychiatric disease worldwide and represents a leading cause of years lived with disability. In turn, this leads to an enormous socio-economic impact. Indeed, MDD represents the costliest psychiatric disorder in Europe (1). Moreover, it has been largely demonstrated that women are nearly twice as likely as men to be diagnosed with MDD. Different biological and environmental factors seem to increase the risk of depression in women; however, this issue remains largely unknown (2).

The main goal of treating MDD is to achieve remission and to maintain the therapeutic effects over time. Despite the availability of different classes of antidepressant drugs, the success of pharmacological treatment is still unsatisfactory, and matching a patient to his/her optimal treatment generally requires multiple trials of different treatments administered adequately in terms of doses and timing, with the sobering observation that the more treatments tried without success, the less likely a successful outcome. Only about 30 and 40% of patients experience remission after the first and second treatment course, respectively, and up to one third of them are classified as resistant to treatment (Treatment-Resistant Depression, TRD) (3, 4). This causes suffering for patients and their families and significantly contributes to pushing up costs for healthcare services.

The observation that TRD occurs despite the high variety of pharmacological drugs acting through different mechanisms of action suggests a possible common mechanism in resistant depression. This is consistent with evidence from studies that combine pharmacology, genetics, and brain imaging data, showing that non-response to a wide range of treatments share common etiology and common neuronal mechanisms that still need to be investigated (5).

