#### Bioinformatic analysis

2.2.6

Quality assessment is done with FastQC, and reads are trimmed using Cutadapt before mapping. For miRNOmic data, sequences with length < 16 nucleotides are discarded. Reads are aligned to the reference genome (hg38 and miRBase v22 for RNASeq and miRNOmic, respectively) with STAR. Counts table is generated using featureCounts, filtered for lowly expressed genes, and analyzed using linear models (limma) for differential expression analysis. Functional analysis utilizes available annotations in functional genomics resources. Network-based approaches are employed to visualize miRNA-target connections and perform gene ontology (GO) analyses. STRINGdb is used for protein–protein interaction retrieval, igraph for network analysis, and clusterProfiler for GO and pathway enrichment analyses. Differential expression of miRNAs is validated by qPCR.

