#### Sample size calculations

2.2.7

Power analyses were assessed using Bioconductor R packages ssizeRNA (20), ssize.fdr (21) and ssize (22). Parameters were obtained from seven publications of expression data in MDD patients (23–29). In cases where adjusted *p*-values were not reported, we adjusted them using the function p.adjust, with the FDR method. Dispersion of genes was not specified in the seven publications so we considered a 0.3 for all of them. Assessed experiments vary considerably in conditions, methods and results, which resulted in sample size estimations per group ranging between 11 and 121. Hence, we aim at a sample size of 150 per group, which exceeds the largest sample size calculated because we want to be conservative for the multi-omic nature of the study, but is also realistic considering our recruitment capacity.

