#### Online surveys

2.4.2

Employing a theory-driven top-down approach, we will further develop surveys to learn about the perspectives of MDD patients, psychiatrists, neurologists, general practitioners, scientists, and the general population in a more hypothesis-driven way. These surveys contain items presented to any participant group as well as target group specific items. For example, all participants are asked to complete a hypothetical decision-making scenario. In this scenario, the algorithm is introduced and participants have to choose. In case patients are addressed in the survey, they are asked whether they would agree to undergo testing. In case health care professionals are addressed, they would be asked whether they would recommend the use of a testing tool for their patients with depression. Completing the surveys, all participants are further asked to rate perceived importance of a set of SDM related variables for this particular decision scenario and to fill in scales meant to operationalize participants’ attitudes, beliefs or perspectives about genetics more generally. All surveys will be provided in English and in the different native languages of the PROMPT-Consortium participating countries and distributed either as a link to a REDCap based online version or as a paper version at all PROMPT Sites (French, German, Italian, Polish and Spanish). Using the R statistical environment (35), we will run linear mixed effect models on a pre-processed and random forest imputed dataset (36). Analyses will be conducted for each participant group, as a whole and in sex-specific manner.

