## Summary and conclusions

3

Our project aims at the development of a clinically useful algorithm model that integrates clinical data (wide range of symptomatology assessment, treatment side effects, presence of childhood trauma) and -omics data (genomic, pharmacogenetic, transcriptomic and miRNomic profiling) for the prediction of treatment response in MDD patients. The study results are framed in the context of precision psychiatry and personalized psychiatry to enable the tailoring of the right therapeutic strategy for the right person at the right time. To account for sex-specific MDD outcomes, all analyses in the project will be stratified according to sex to better understand the sex dimension of treatment response both in relation to biological factors, sex-related lifestyle and environmental factors. Moreover, our project deepens the knowledge and experience of the shared decision making process when using predictive algorithms to aid decision making in Psychiatry. Both, predictive computational tools and shared decision making processes constitute key components of the Personalized Psychiatry concept. The definition of TRD that we used is the commonly accepted clinical definition of two or more failed pharmacological treatments. Unfortunately, the absence of a validated definition of TRD is a major limitation from the viewpoints of translational research, treatment development, as well as clinical and policy decision-making. Indeed, for example neurostimulation techniques and evidence-based psychotherapy are not considered in the definition of TRD, which is a limitation of this definition. TRD patients should include particularly the non-remitters and recurrent MDD patients having a high probability to have a poor prognosis of the disorder. The pathway toward more targeted treatments in psychiatry requires a more precise delineation of the phenotype being evaluated, and this represents an important goal for current and future research in psychiatry.

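### Sex-stratified limma tests are the stated route to the influence of sex on TRD, but they do not test whether the TRD-versus-responder difference differs between men and women

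*Protocol article*

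**What the plan says.** Section 2.2.8 (Integration of clinical and omics data) states that "we will stratify all analyses according to sex. This might as well help to further decipher the influence of sex on TRD". The Summary and conclusions (section 3) repeats the link without the hedge: "all analyses in the project will be stratified according to sex to better understand the sex dimension of treatment response". The feature-level method is given in section 2.2.6, where counts are "analyzed using linear models (limma) for differential expression analysis". No section names a group-by-sex term or any other comparison of effects between men and women.

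Two other statements fix the numbers available. Phase 1 planning (section 2.2.7) says "we aim at a sample size of 150 per group", both sexes together, and section 2.2.8 says "this discovery analysis is done on two thirds of the Phase 1 data". For the surveys, section 2.4.2 says "Analyses will be conducted for each participant group, as a whole and in sex-specific manner".

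**The concern.** The aim and the test have different null hypotheses. In a within-sex limma analysis the null is that TRD patients and responders do not differ in that sex. For a statement about the influence of sex, the null is that the TRD-versus-responder difference is equal in the two sexes. Two within-sex tests, taken as they stand, leave the second null untested.

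The risk lies in the next step. Significance in women and non-significance in men is not evidence of a sex difference, because each result depends on the power in its own stratum. A marker with the same effect in both sexes can then be reported as sex-specific. If women predominate in the sample, most such markers would appear female-specific.

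**Working it through.** **Planning figure.** Section 2.2.7 reports that the seven source publications "resulted in sample size estimations per group ranging between 11 and 121". This range cannot be reproduced, because effect sizes, FDR level and power are not given. It serves below only to anchor a plausible effect size.

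**Inputs.**
- Discovery set: two thirds of 150 per group, so 100 TRD and 100 responders (sections 2.2.7 and 2.2.8).
- Sex split: not given for this cohort. The Introduction says "women are nearly twice as likely as men to be diagnosed with MDD". That is a diagnosis rate, so 2:1 is only a proxy. Range used: 1:1 (50 women and 50 men per response group) to 2:1 (67 and 33).
- Alpha and effect size: not given. Assumed alpha 0.05 and 0.001 (the latter as a rough stand-in for a multiplicity-adjusted threshold), and standardized effect d from 0.3 to 0.8, equal in both sexes.
- Normal data and ordinary two-sample t-tests, as an approximation to limma's moderated tests.

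**Formula.** Let Pf and Pm be the noncentral-t power in women and men, with noncentrality d × √(n/2). Then

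P(significant in exactly one sex) = Pf(1 − Pm) + Pm(1 − Pf).

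**Example: 67/33, d = 0.5, alpha 0.05.** Pf = 0.819 and Pm = 0.516. Women only: 0.819 × 0.484 = 0.396. Men only: 0.516 × 0.181 = 0.093. Sum: 0.49.

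**Probability that a common effect is significant in exactly one sex**

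| d | alpha 0.05, 1:1 | alpha 0.05, 2:1 | alpha 0.001, 1:1 | alpha 0.001, 2:1 |
|---|---|---|---|---|
| 0.3 | 43% | 45% | 7% | 7% |
| 0.5 | 42% | 49% | 31% | 36% |
| 0.7 | 12% | 21% | 50% | 61% |
| 0.8 | 4% | 11% | 40% | 56% |

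The result does not need the 2:1 assumption; it is present at 1:1. It falls for large effects at alpha 0.05, where both sexes detect them, and for small effects at alpha 0.001, where usually neither does.

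**Anchoring d to the largest planning figure.** The effect with 80% power at 121 per group is d = √(2/121) × (z for alpha + 0.842). This is 0.1286 × (1.960 + 0.842) = 0.36 at alpha 0.05, and 0.1286 × (3.291 + 0.842) = 0.53 at alpha 0.001. With normal-approximation power in the discovery set, the exactly-one-sex probability is 49% (1:1) to 52% (2:1) at alpha 0.05, and 39% to 44% at alpha 0.001.

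**Direct test of the sex difference.** With equal true effects, a group-by-sex contrast rejects at its nominal rate: 0.048 to 0.051 in simulation at alpha 0.05. Its power at 67/33 follows from SE = √(2/67 + 2/33) = 0.301 in standardized units, by normal approximation:
- d = 0.8 in women and 0 in men: 0.8/0.301 = 2.66. Power is 76% at alpha 0.05 (2.66 − 1.96 = 0.70) and 26% at alpha 0.001 (2.66 − 3.29 = −0.63).
- Opposite effects of 0.5, a difference of 1.0: 1.0/0.301 = 3.32. Power is 91% at alpha 0.05 and 51% at alpha 0.001.
- A difference of 0.36: 0.36/0.301 = 1.20. Power is about 22% at alpha 0.05.

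**The case against.** The strongest reply is that the article never says significance lists will be compared between the sexes. A reader might infer that the project will label a feature sex-specific because it is significant in one sex only, and that its sex conclusions will mostly reflect stratum size. The text does not support that. Section 2.2.8 says only that stratifying might help, and stratified fits yield an estimate and standard error per sex. Their difference over its standard error is essentially the interaction test, so stratifying does not prevent the right comparison. This stands, and it makes the figures above conditional on how the results are read.

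Three further limits also stand:
- The argument concerns limma, and the survey mixed models if sex differences are claimed there. WGCNA, MOFA, iClusterPlus and PLS-DA are not within-sex significance tests of this kind.
- Sex is not the core objective. The predictive model is judged on held-out Phase 1 data and on Phase 2, including by sex (section 2.3.6). Nothing says that separate sex-specific feature sets enter it.
- A predominance of false female-specific findings would need an excess of women, and the cohort's split is not stated.

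It may also be said that an unnamed contrast is detail left to a full plan. This does not dispose of the point. The article states an aim and names a method for it, twice, and that method alone does not test the aim. Reading stratification as adjustment for sex does not help, since adjustment does not test a sex difference either. The tree-based models of section 2.2.9 can use interactions if the sexes are pooled, but they give no error-controlled test of one.

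**Conclusion.** The point holds as a mismatch between a stated aim and the method named for it. Within-sex limma tests do not establish whether the TRD-versus-responder difference depends on sex. If they are read by which sex reaches significance, a common effect of d = 0.5 would look sex-specific with probability 42–49% at alpha 0.05 and 31–36% at alpha 0.001. The problem is small for small effects at a strict threshold (about 7% at d = 0.3, alpha 0.001) and for large effects at alpha 0.05 (4–11% at d = 0.8). These figures rest on the two-thirds discovery set, a sex split between 1:1 and 2:1, equal true effects, and assumed alpha and d. They do not predict what share of reported sex findings would be wrong, which depends on the unknown mix of true effects.

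**What to change.** In section 2.2.8, fit one limma model to both sexes with response group, sex and their interaction, or formally contrast the two within-sex estimates. Base any claim of a sex difference on that contrast, under FDR control and with its confidence interval. Keep the within-sex results as descriptive, and state that significance in one sex only is not evidence of a difference. In section 2.4.2, use the corresponding sex interaction term in the survey mixed models if sex differences are to be claimed there.

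The cost is one contrast and some wording, with no new patients or data. The real price is power: as shown above, even a large sex difference is likely to be missed at a strict threshold. Few sex differences will be claimed, and the plan should say that a non-significant interaction does not show that the sexes are alike.

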#### Development of the predictive algorithm

2.2.9

We will combine the multi-omic features identified to play a role in TR to generate a predictive model for TRD on Phase 1 data using state-of-the art statistical and machine learning methods for classification. We favor tree-based methods such as random forests or extreme gradient boosting over traditional regression models because they are not equipped to identify complex interacting risk structures empirically and have failed to model sex-specific associations (31). Standard methods of internal validation (e.g., bootstrap or cross-validation) will be used to estimate performance, to avoid over-fitting and to ensure reproducibility of the model. To select between models, we will use standard metrics such as Accuracy and F-measure on the validation set. Potential biases that may affect the inclusiveness of the models (e.g., sex or ethnicity issues) will be carefully considered.

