### Study design

2.1

The overall methodology of the project is based on a two-phase design (Figure 1). In the first phase (training phase, retrospective design), 300 already recruited MDD patients, including 150 TRD and 150 responders considered as extremes phenotypes of response, will undergo a deep clinical and omics profiling. These data will be exploited to develop an innovative integrative algorithm for the prediction of MDD treatment outcome.

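### Outcome-based feature discovery comes before the resampling, and models are chosen on an undefined validation set; followed in that order, at least one Phase 1 performance estimate is optimistic

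*Protocol article*

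**What the plan says.** Phase 1 uses "300 already recruited MDD patients, including 150 TRD and 150 responders considered as extremes phenotypes of response" (section 2.1). Section 2.2.8 lists the discovery methods. Limma differential expression between the two groups and PLS-DA, which the article itself describes as supervised, use the outcome labels. On the split it says that "this discovery analysis is done on two thirds of the Phase 1 data, keeping one third unseen from any training process".

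Section 2.2.9 then begins from features that already exist: "We will combine the multi-omic features identified to play a role in TR to generate a predictive model for TRD on Phase 1 data". It does not say which part of the Phase 1 data. On performance: "Standard methods of internal validation (e.g., bootstrap or cross-validation) will be used to estimate performance, to avoid over-fitting". On the choice between candidates: "To select between models, we will use standard metrics such as Accuracy and F-measure on the validation set".

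No Phase 1 section defines the validation set, says which patients the resampling covers, or says whether discovery is repeated inside the folds or bootstrap samples. After section 2.2.8 the held-out third is not mentioned again by name. Sections 2.3 and 2.3.6 then test the resulting algorithm in a new cohort of 300 patients.

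**The concern.** Cross-validation or bootstrap is honest only if everything that looked at the outcome is repeated within each resample. If features are picked by comparing TRD patients with responders in some 200 patients, and those same patients are then split into folds, each test fold has already helped to choose the features. The fold score is then high even when there is no signal.

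A second problem arises if the validation set is the held-out third. Choosing between models is a training step, so the winner's score on that third is a best-of-several score, and the third is no longer kept as described ("keeping one third unseen from any training process").

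What is at stake is the Phase 1 performance figure and possibly the choice of the algorithm that goes into Phase 2. An inflated Phase 1 figure also makes Phase 2 harder to interpret. A drop in performance could come from the inflation or from the move from extreme phenotypes to a naturalistic cohort, and the two could not be told apart.

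**Working it through.** The article gives no Phase 1 performance figure, so there is none to reproduce. The check covers the possible readings first and then the size of each bias.

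**Readings of the validation set**

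- *Folds or out-of-bag samples within the two thirds, features fixed.* The labels of these patients chose the features, so the scores and any model choice based on them are contaminated. The third stays clean.
- *The held-out third.* Its score is a best-of-K score, and section 2.2.8 is contradicted. Any cross-validation on the two thirds with fixed features is still contaminated.
- *Resampling over all Phase 1 data*, which section 2.2.9 permits. Two thirds of the patients are contaminated and the third enters training.

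The order as written escapes only if discovery is repeated inside every resample. That is not excluded, but it is not the order described.

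**Inputs from the article:** 300 patients, 150 per group; discovery set 300 × 2/3 = 200; held-out set 300 × 1/3 = 100.

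**Assumptions (not in the article):** independent noise features; P screened; k kept; K candidate models; correlation between models.

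**(a) Cross-validation after selection.** Pure noise, true accuracy 0.50. The top k features by a t-like statistic on the 200 patients, nearest-centroid classifier, 10-fold cross-validation, 25 repetitions per setting:

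| P | k | CV after selection | Selection inside folds | Held-out third |
|---|---|---|---|---|
| 1,000 | 20 | 0.77 | 0.52 | 0.49 |
| 1,000 | 100 | 0.87 | 0.50 | 0.50 |
| 10,000 | 20 | 0.83 | 0.51 | 0.51 |
| 10,000 | 100 | 0.97 | 0.52 | 0.50 |
| 20,000 | 20 | 0.86 | 0.50 | 0.50 |
| 20,000 | 100 | 0.98 | 0.51 | 0.51 |

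The excess over the truth runs from 0.77 − 0.50 = 27 points to 0.98 − 0.50 = 48 points. A separate simulation on the AUROC scale (200 patients, 10,000 noise features, top 50 kept, ridge score, 5-fold cross-validation, 40 runs) gave a mean of 0.97 (range 0.95 to 0.99), against 0.50 with selection inside the folds. Discovery on the two thirds does not by itself bias the held-out third.

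**(b) Best of K models on the held-out 100.** For K equally good models whose scores have correlation r, the expected excess is about e(K) × SD × √(1 − r), where e(K) is the expected maximum of K independent standard normals: e(10) = 1.54 and e(20) = 1.87. At true accuracy 0.70, SD = √(0.7 × 0.3/100) = 0.0458.

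- K = 10: 1.54 × 0.0458 = 0.071 for r = 0; × √0.2 = 0.032 for r = 0.8.
- K = 20: 1.87 × 0.0458 = 0.086 for r = 0; × √0.2 = 0.038 for r = 0.8.

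That is about 3 to 9 points. A direct simulation of correct and incorrect calls (4,000 repetitions, true accuracy 0.70, correlation 0.8 down to 0) gave 4.5 to 6.8 points for K = 10 and 5.5 to 8.3 for K = 20. Its values at 0.8 are higher because the correlation there is set on an underlying normal scale, which leaves the binary calls less correlated. At accuracy 0.50 the binary correlation is (2/π) × arcsin(0.8) = 0.59, and 1.54 × 0.05 × √0.41 = 0.049, as simulated. Over K = 2 to 20 and true accuracies 0.5 to 0.8, the simulated range is 1.4 to 9.3 points.

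**The case against.** The strongest reply is that the article nowhere says that features are frozen before resampling, or that models are picked on the held-out third. The sentence just before the one on model choice names bootstrap and cross-validation, so the validation set may mean validation folds, and nesting is a detail that a condensed article can leave to a fuller plan. Even if the third is used for model choice, the layout is then an ordinary train, validate and test design with Phase 2 as the test.

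Much of this stands. A reader might infer that models are certainly chosen on the held-out third and that both Phase 1 estimates are therefore biased. The text does not support that certainty, and on the fold reading the third stays clean. A reader might also infer that a pure-noise model will be locked for Phase 2. That does not follow: such a model scored 0.49 to 0.51 on a clean third, and even the best of 20 independent noise models would reach only about 0.50 + 0.093 = 0.59 there. Nor is all discovery label-based, since the article does not say that WGCNA or MOFA use the outcome.

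The reply does not remove the point. The article states an order of steps and offers the resampling as the guard against over-fitting. Carried out in that order on the discovery patients, it does not provide that guard. This is a stated sequence that gives a wrong estimate, not merely missing detail.

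**Conclusion.** The point holds in a conditional form. Followed as written, sections 2.2.8 and 2.2.9 make at least one Phase 1 performance estimate optimistic, and possibly two.

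The two biases differ greatly in size. Resampling after selection is the large one, at 27 to 48 accuracy points on pure noise. This shows the mechanism and does not forecast this project, because it assumes independent features, no true signal and the stated P and k. Bootstrap with fixed features is open to the same argument but was not simulated. Selection on the held-out third is worth about 3 to 9 points for an assumed 10 to 20 models at true accuracy 0.70, and it matters only if that third is the validation set. In that case it also conflicts with section 2.2.8.

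A reader might take this as a flaw in the Phase 2 validation. It is not: a model locked before Phase 2 is tested there without this bias. What is affected is the Phase 1 estimate and possibly which model is carried forward.

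**What to change.** 1. Define the validation set in section 2.2.9 and say which patients the bootstrap or cross-validation covers.
2. Repeat every label-using step inside the resampling on the two thirds: the differential-expression filter, PLS-DA, feature selection and tuning. Make the choice between models there too, on inner resamples.
3. Lock one model, then score it once on the held-out third.
4. Report the nested estimate and the one-time hold-out estimate as Phase 1 performance, and take the locked model into Phase 2.

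The cost is more computing time, some rewording, and a Phase 1 performance figure that will probably be lower. No new patients or assays are needed.
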